## Methods/design

This prospective, observational cohort study will evaluate short- and long-term effects in post-menopausal patients given the choice to undergo PSO or not during surgery for CRC. As such, two separate cohorts are studied based on the patient’s preference. Cohort 1 includes all patients who had PSO, while cohort 2 includes all patients who did not choose PSO. All patients are followed up prospectively.

### Current practice and study setting

In 2020 an information bulletin and decision guide (Additional file 1) on PSO was implemented in several Dutch hospitals for female patients ≥ 60 years of age. In patients that opted for PSO, prophylactic surgery during CRC will be performed by surgeons, gynecologists, or both (depending on the surgeons’ experience and local hospital policies).

Post-decision outcomes are collected prospectively with standardized variables and data are stored in electronic patient files. These variables will be used for various statistical analyses and will provide evidence as to whether or not PSO adds significant value to postmenopausal CRC patients.

The following website lists all hospitals that contributed patients to this study: https://romic.surgery/ziekenhuizen/.

### Study population and eligibility criteria

All female patients with CRC who received the information bulletin and decision guide and who signed informed consent (IC) for use of follow-up data are included in this study cohort. Patients are also included when they answered positively to the ‘opt-in’ question for research and education within their electronic health record. Figure 1 shows schematic representation of the study cohort.

**Fig. 1 Fig1:**
[figure not shown]
Schematic representation of the cohort. PSO = prophylactic salpingo-oophorectomy

#### Inclusion criteria

• Female sex• Age ≥60 years at the time of CRC diagnosis• Intended curative resection of colon or rectal cancer, with no evidence of incurable distant metastases• Informed consent (Additional file 2) or consent by opt-in form (for research and education)

#### Exclusion criteria

• No signed informed consent and no consent by opt-in form (for research and education)• Surgery with palliative intent• Known distant metastases preoperatively, or evidence of distant or intraperitoneal metastases during operation, except when curative metastasectomy is considered possible (e.g. for hepatic metastases)

#### Who will obtain informed consent and how

Written, informed consent to participate will be obtained from all participants or, in cases where a positive answer for opt-in (for research and education) exists, data can be used without a written informed consent form. Researchers, registration officers, case managers and/or surgeons will obtain the informed consent.

#### Additional consent provisions for collection and use of participant data and biological specimens

Not applicable.

### Intervention description

This study protocol is not designed for the implementation of a procedure. However, it will be used to evaluate the effect of an existing procedure implemented in the local CRC pathway as follows: PSO *vs*. non-PSO in a female population with CRC. The following items are therefore not applicable: criteria for discontinuing or modifying allocated interventions, strategies to improve adherence to interventions, relevant concomitant care permitted or prohibited during the trial and provisions for post-trial care.

### Randomization, blinding and treatment allocation

Because this study will evaluate the effects of PSO that are facilitated by an altered CRC care pathway, randomization and blinding are not applicable. The two different patient groups are formed based on patient preferences.

### Study procedures

Complications will be scored according to the Clavien-Dindo classification [36, 37]. Furthermore, the Comprehensive Complication Index [38] is a composite score that summarizes the patients’ postoperative wellbeing regarding complications based on the Clavien-Dindo classification. Both scores will be determined after surgery.

Health-related quality of life (HRQL) will be measured using EORTC QLQ-C30 for cancer patients in general, and EORTC QLQ-CR29 specifically for CRC patients. The outcomes will be measured at baseline, at 3 months, and at 1-, 2-, and 3-year(s) after surgery. Differences in outcomes between the two groups will be analyzed statistically.

### Participant timeline

Patients in this study will be enrolled during the period from 07/01/2020 to 07/01/2025. The follow-up period will be 5 years. When a patient withdraws from the study, only the data collected until that time will be used.

### Sample size

The primary study outcome is the occurrence of either CRC metastases in the ovaries or primary ovarian cancer within 3 years after resection of the (primary) colorectal tumor. Based on previous studies, we assume the incidence of synchronous and metachronous colorectal metastases in the ovaries will be 2.0% during the follow-up period [15, 17, 21]. The incidence of primary ovarian cancer is expected to be 0.1% in this period [39]. This gives an overall incidence of 2.1% in cases where PSO is not performed (non-PSO group).

Following PSO, colorectal tumors can no longer metastasize to the ovaries, while the incidence of primary ovarian malignancy should presumably be 0% (PSO group). However, a small risk of primary ovarian malignancy still exists after PSO due to the development of ‘ovarian remnant syndrome’ (ORS) [40–42]. This risk is estimated to be approximately 0.01% for the PSO group.

Based on these assumptions and an alfa of 0.05 with power of 80%, a sample size calculation was performed using an online sample size calculator for comparison of two proportions [43]. This gave a sample size of 371 patients per group, or 742 in total.

Since all eligible patients are not randomized, it is necessary to correct for possible confounders. According to the one-in-ten rule, at least 10 events (of ovarian malignancies) are needed per factor studied in order to achieve sufficient statistical power [44]. Besides PSO, correction will also be made for age as another possible confounder.

Based on current clinical practice, we estimate that about half of all postmenopausal CRC patients undergo PSO during resection of their colorectal tumor. Therefore, we expect the two study groups to be approximately equal in size. The estimated incidence of ovarian malignancies in the total study population will thus be 1.055% (average of 2.1% and 0.01%), thus requiring a sample size of at least 1896 patients (20/0.01055).

Finally, after taking into account a dropout rate of 5%, at least 1996 patients should be recruited into the study.

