#### Statistical analysis of the primary study parameters

For each group, the number of patients who are alive and without evidence of disease relapse after 3 years of follow-up will be determined. Kaplan–Meier curves with the end-point of disease-free survival will be constructed and the log-rank test will be used to compare 3-year disease-free survival rates between groups.

In the case of differences in baseline variables between the two groups, Cox regression analyses including these variables will be performed. Univariate analysis will first be used to identify possible confounders. Multivariate Cox regression analysis will then be performed including ‘group’ (PSO or no PSO), with possible confounders as independent variables and disease-free survival as the dependent variable.

The NNT to prevent one case of ovarian cancer will be calculated according to the method of Lubsen et al*.* [35]. NNT describes the number of patients required to undergo PSO in order to gain 1 year of disease-free survival.

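### Twenty pooled events do not secure an estimable age-adjusted PSO effect, because the protocol's own rates put about 99.5% of them in the non-PSO group

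*Protocol article*

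**What the plan says.** All of the sizing is in the Sample size section of the Protocol article. For the non-PSO group: "This gives an overall incidence of 2.1% in cases where PSO is not performed (non-PSO group". For residual risk after PSO: "This risk is estimated to be approximately 0.01% for the PSO group". A two-proportion calculation follows ("Based on these assumptions and an alfa of 0.05 with power of 80" per cent), with the result "This gave a sample size of 371 patients per group, or 742 in total".

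The section then notes that patients are not randomised, so confounding must be dealt with, and states that "at least 10 events (of ovarian malignancies) are needed per factor studied in order to achieve sufficient statistical power". The factors are counted as two: "Besides PSO, correction will also be made for age as another possible confounder". Equal groups are expected, and the two rates are averaged: "The estimated incidence of ovarian malignancies in the total study population will thus be 1.055% (average of 2.1% and 0.01" per cent. Dividing 20 events by that average gives 1896, and a 5% dropout allowance gives 1996.

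The section does not mention how the 20 events divide between the groups. The article names no exact, penalised or other sparse-data method for the adjusted comparison. The adjusted PSO-plus-age analysis of ovarian malignancy is implied only here. The Cox model in the section on the primary study parameters ("In the case of differences in baseline variables between the two groups, Cox regression analyses including these variables will be performed") has disease-free survival as its outcome. The logistic models planned for secondary parameters concern complications, intra-abdominal relapse and primary ovarian cancer, not the composite of metastatic and primary ovarian malignancy.

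**The concern.** Adjustment for confounding is the only stated reason for recruiting 1996 patients rather than 742. Groups form by patient preference, so the adjusted comparison carries much of the inference about PSO.

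The one-in-ten rule guards against unstable or overfitted coefficients. It does not measure power. Its usual reading also takes for granted that events occur at both levels of a binary factor, whereas here the protocol assumes almost none in one group. Averaging 2.1% and 0.01% to 1.055% hides this. When one level of a binary covariate has no events, the likelihood keeps rising as its coefficient goes to minus infinity. This is separation: there is no finite odds or hazard ratio, and Wald standard errors become meaningless.

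The practical risk is that the sizing step meant to support a confounder-adjusted PSO effect leads, most of the time, to a model that cannot report one and gives no usable ratio from which to derive an adjusted NNT.

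**Working it through.** **Inputs (Sample size section).** Event rates: non-PSO 0.021, PSO 0.0001. Alpha 0.05 and power 80%, taken as two-sided because that reproduces the stated size. Two factors, 10 events each. Groups about equal. Dropout 5%.

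1. **The protocol's own figures reproduce.**
   - Two proportions, unpooled variance: n = (1.960 + 0.842)² × (0.021 × 0.979 + 0.0001 × 0.9999) / (0.0209)² = 371.2, the stated 371 per group.
   - Pooled incidence: (0.021 + 0.0001)/2 = 0.01055. Then 20/0.01055 = 1895.7, so 1896.
   - Dropout: 1896/0.95 = 1995.8, so 1996.

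2. **Where the events fall, at 1896/2 = 948 per group.**
   - Non-PSO: 948 × 0.021 = 19.91.
   - PSO: 948 × 0.0001 = 0.095.
   - Share in the non-PSO group: 19.91/20.00 = 99.5%.
   - P(no PSO event) = (1 − 0.0001)^948 = 0.910.
   - At 998 per group: 20.96 events, 0.0998 events and 0.905.

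3. **What an ordinary adjusted model does.** A logistic model with PSO and a simulated age covariate, fitted to 20/948 versus 0/948, gave a PSO coefficient of −23 to −26 depending on the fitting routine, standard errors of 10⁴ to 10⁵, and Wald p of at least 0.998. In 1000 simulated studies at the protocol's rates (assumed: no age effect on outcome, mean age 0.3 SD lower in the PSO group), 90.6% had no finite PSO estimate.

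4. **Power for the PSO contrast at 948 per group.**

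| Test | Power |
|---|---|
| Normal approximation, unadjusted | 99.4% |
| Fisher exact, unadjusted | >99.9% |
| Likelihood ratio, unadjusted | >99.9% |
| Wald, unadjusted | 9.0% |
| Likelihood ratio, PSO + age (simulated) | about 100% |
| Firth penalised likelihood ratio, PSO + age (simulated) | about 100% |
| Wald, PSO + age (simulated) | 9.3% |

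   The Wald figure is essentially the chance of at least one PSO event, 1 − 0.910 = 0.090.

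5. **More patients would not cure it.** Ten expected events in the PSO group need 10/0.0001 = 100,000 PSO patients.

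6. **Sensitivity to the 0.01% figure (assumed range, not from the article).** P(no PSO event among 948) is 62% at 0.05%, 39% at 0.1% and 15% at 0.2%.

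7. **The absolute scale copes.** For 20/948 versus 0/948 the risk difference is 2.11%. Wilson limits are 1.37% to 3.24% for 20/948 and 0 to 0.40% for 0/948. Newcombe lower limit: 2.11 − √((2.11 − 1.37)² + 0.40²) = 1.27%. Upper limit: 2.11 + (3.24 − 2.11) = 3.24%. Inverting gives NNT 47 (31 to 79).

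**The case against.** The strongest reply has four parts.

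- **Power.** A reader might infer that the study lacks the power the section claims. The documents do not support this. The target far exceeds the 742 that give 80% power unadjusted, and every test in the table except Wald has power above 99%. The article names no Wald test for this comparison. This part of the reply stands in full.
- **Other models.** A reader might also infer that the disease-free survival Cox model will separate, or that the roughly 15 baseline variables in Table 2 overrun a 20-event budget. Neither follows. Disease-free survival counts relapse and death generally, so the 19.9 versus 0.095 split does not apply, and the 20-event count was made for a different outcome.
- **Metrics.** Table 1 lists incidence and NNT as the primary metrics. Both can be estimated with no PSO events, so the unadjusted primary result is safe. This stands, and limits the problem to the adjusted ratio.
- **Level of detail.** Choice of penalisation and interval is commonly left to an analysis plan that is not shown. True, and its absence is not the point here. The point is that the article does state a sizing rule and its rationale, and the rule does not deliver what it is invoked for.

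**Conclusion.** The concern holds as a fault in the sizing rationale and in the adjusted estimate it is meant to support. Under the protocol's own rates and equal groups, an ordinary maximum-likelihood PSO coefficient adjusted for age would be non-finite about nine times in ten. Describing 10 events per factor as securing power is wrong in kind: the rule is not a power criterion, and here it does not secure stability for the coefficient of interest either.

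The conclusion does not extend to low power, to the disease-free survival analysis, or to the unadjusted incidence and NNT. It rests on the 0.01% rate after PSO; at higher true rates separation becomes less frequent, as the sensitivity range shows. It also assumes the implied adjusted analysis would be ordinary logistic or Cox regression, since the article does not state its form.

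**What to change.** For the confounder-adjusted analysis of 36-month ovarian malignancy, specify one of the following:

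- an adjusted risk difference, for example stratified or weighted by a propensity score for choosing PSO, with an interval that remains valid at zero events; the NNT follows by inversion; or
- Firth-penalised logistic or Cox regression with profile-likelihood intervals and tests, if a ratio is wanted.

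In the Sample size section, remove the statement that 10 events per factor gives sufficient power. Keep 1996, but justify it by the expected precision of the risk difference and NNT, using the unadjusted benchmark of 2.1% (1.3% to 3.2%) and NNT 47 (31 to 79) at 948 per group.

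The cost is revised wording and modest extra analysis work. No additional patients or data are needed.

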#### Recruitment

Consecutive CRC patients will be checked for eligibility by their surgeons once they are scheduled for tumor resection surgery. Either the surgeon or the case manager (depending on local logistics) will inform eligible patients about the study at their next visit to the outpatient clinic and provide them with written information. All patients will receive the same written information on the specific issues concerning the study.

Written informed consent for inclusion in follow-up will then be sought from the patient by the involved surgeon or case manager. After informed consent is given, patients are registered with a code (no personal identifiers) in an online case record form using Research Manager [45].

### Data collection and management

#### Plans for assessment and collection of the outcomes

Standardized variables used in the pre-operative records and standardized items during surgery will be used to record the outcomes. An electronic data collection form will be used to capture the information. Participants will be followed up at 3 months and at 1-, 2-, and 3 year(s) after surgery. At each follow-up time, the physician will note whether complications (within ≤ 3 months postoperatively) or recurrent disease have occurred.

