**Secondary**		
Disease-free survival	DFS	36 months
Number needed to treat with PSO to prevent one case of ovarian cancer (primary or metastatic)	NNT	36 months
Surgery-related morbidity of PSO	Number	36 months
Subsequent intra-abdominal relapse pattern in the non-PSO group	Number	36 months
Abnormal ovaries found during surgery	Number	During surgery
Incidence of ovarian (micro)metastatic disease	Incidence	36 months
Quality of life (EORT QLQ-C30 and EORTC QLQ-CR29)	SUM score	Baseline, 3-, 12-, 24- and 36 months
Repeat surgery for complications (i.e. adhesions)	Numbers	36 months
Long-term overall survival	OS in days	60 months
Preference for PSO	Numbers	36 months
Reversal of decision	Numbers	36 months
Baseline characteristics	Numbers	Before surgery

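### The follow-up rule records complications only to 3 months, so it does not capture the late morbidity and adhesion surgery that Table 1 sets at 36 months; it also lists no contact for the 60-month survival outcome

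*Protocol article*

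**What the plan says.** Four parts of the protocol article bear on this point.

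- **Plans for assessment and collection of the outcomes.** The contacts are listed: "Participants will be followed up at 3 months and at 1-, 2-, and 3 year(s) after surgery". The content of each contact follows: "the physician will note whether complications (within ≤ 3 months postoperatively) or recurrent disease have occurred".
- **Table 1, secondary outcomes.** "Surgery-related morbidity of PSO" has a time point of 36 months. A separate row, "Repeat surgery for complications (i.e. adhesions", also has 36 months. "Long-term overall survival" is measured in days with a time point of 60 months.
- **Secondary objectives.** These ask about operations for abdominal adhesions up to 3 years, and about the effect of PSO on overall survival at 5 years.
- **Participant timeline.** "The follow-up period will be 5 years".

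Three further statements are relevant. Under Study procedures, the Clavien-Dindo grade and the Comprehensive Complication Index are determined after surgery, with no later time point. Under Current practice and study setting, outcomes are gathered prospectively and held in electronic patient files. The section on participant retention says that follow-up is routine care and that no further retention measures are planned.

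**The concern.** The collection section names two things that the physician records at a contact: complications in the first 3 months, and recurrence. The outcome table asks for surgical morbidity and re-operation over 36 months. If the case record form is built to the collection section, a patient who has an adhesion operation in the second year is seen at 24 months, but nothing that the rule names prompts the event to be entered.

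These are the harms to be set against the benefit. The Discussion says that the study will inform on the long-term effects of both strategies on complications, so that patients can weigh them. On the planning rates in the Sample size section, the absolute benefit is small: 2.1% against 0.01%, or about one ovarian malignancy prevented per 48 procedures (1/0.0209 = 47.8; this follows from the protocol's assumptions and is not a figure that it states). With a benefit of that size, even infrequent late harm affects the balance, and under-counting it would favour PSO in that weighing.

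The survival outcome raises a second, lesser question. Its horizon is 2 years beyond the last listed contact, and the text does not say how vital status is obtained in that interval.

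**Working it through.** No sample size, power or alpha depends on this point. The check is a comparison of stated time points.

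**Step 1: what a contact records, against what Table 1 needs.**

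| Outcome (Table 1) | Time point | Named in the collection rule? |
|---|---|---|
| Surgery-related morbidity | 36 months | Only if it occurs by month 3 |
| Repeat surgery for complications (adhesions) | 36 months | Not named; falls under complications only if it occurs by month 3 |
| Overall survival | 60 months | No contact listed after month 36 |

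**Step 2: a test case.** Take an adhesion operation at month 14. It lies within the 36-month row of Table 1 and the 3-year secondary objective. It is later than 3 months, so the complications item excludes it. It is not recurrent disease, so the other item excludes it as well. The patient has contacts at 12, 24 and 36 months. The gap therefore lies in the item recorded and its window, not in a lack of contacts.

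**Step 3: whether another section closes the gap.** The complication scores under Study procedures are determined after surgery, with no later time point, so they do not extend the window. The electronic patient files could contain the operation, but no section defines which late events are to be looked for in them.

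**Step 4: length of the gaps.**

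- Morbidity and re-operation: 36 − 3 = 33 months of the Table 1 window fall outside the complications item.
- Survival: 60 − 36 = 24 months of the horizon have no listed contact. The 5-year period in Participant timeline (5 × 12 = 60 months) does match the survival row. The mismatch is thus between that section and the list of contacts.

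These are lengths of calendar time. The document gives no rate for late complications or adhesion surgery, so they cannot be converted into numbers of missed events.

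**Step 5: the primary outcome.** Its time point is 36 months and the last listed contact is at 3 years, so the contact schedule reaches it.

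**The case against.** The strongest reply is that the collection section does not claim to be exhaustive. The 3-month parenthesis may simply define postoperative complications for the two complication scores, and repeat surgery is a separate row with its own 36-month window. Outcomes are held in electronic patient files, local data managers handle the data, and a data management plan exists. Lists of form fields and the source of vital status are details that an article commonly leaves to such documents.

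Much of this stands for survival. The article does state 5 years of follow-up, and a date of death needs no study visit. A reader might infer that follow-up ends at 3 years, or that 60-month survival cannot be obtained. The documents support neither. What remains is an inconsistency between the timeline and the list of contacts.

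It stands less well for late harm. The printed rule puts a limit on the complications noted at every contact, and that limit conflicts with the printed time points for morbidity and re-operation. This is a conflict between statements, not an omitted detail. If the 3-month limit was meant only for the scores, the section should say so. A later search of records remains possible, so these outcomes are not unobtainable either. But an undefined search gives no assurance that all hospitals would look for the same events.

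A reader might also infer informative censoring of survival. The documents do not show it: if every patient were censored at 3 years, that would be administrative censoring. Nor is a difference in under-counting between the groups shown, since the 3-month window applies to both.

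**Conclusion.** The point holds as an inconsistency to be corrected before the outcomes are collected and analysed. Its main part is late harm: as written, the collection rule does not capture surgical complications or adhesion operations in months 4 to 36, although one objective and two Table 1 rows require them. A form built to that rule would under-count late harm. The lesser part is survival: no contact is listed for months 36 to 60, while Table 1, the secondary objectives and the timeline all point to 5 years.

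Three Table 1 rows are affected, all secondary. The conclusion assumes that the case record form follows the collection section as printed; if it already has dated re-operation fields, only the text needs correcting. A reader might express the gaps as 92% (33/36) and 40% (24/60) of the outcomes lost. Those are shares of calendar time, not of missed events, and the document allows no estimate of the latter.

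**What to change.** 1. In the collection section, have each of the existing 12-, 24- and 36-month contacts record late surgery-related complications and any abdominal re-operation, with date and indication. Keep the 3-month window only for the Clavien-Dindo and Comprehensive Complication Index scores, and say so.
2. State that vital status at 60 months, with date of death where applicable, is extracted from routine records in the same way for every patient in both groups. No recurrence extraction at 60 months is needed for this purpose, because disease-free survival is set at 36 months.
3. Reconcile Table 1, the secondary objectives, the participant timeline and the collection section so that each outcome has one window and one source.

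The cost is a few form fields, one records check per patient at 5 years, and the small data-entry burden that these bring. No extra visit or procedure is needed.
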